#### **8.2.4 Post-treatment assessments**

Only if it has been reported any adverse event that may be under way in the last visit or, if the patient had presented a viral load > 50 copies / mL at that visit, a telephone follow-up call will be made after 30 days of last visit study to monitor safety.

#### **8.2.5 Early study discontinuation**

In the event of early discontinuation, the subject should return to the site as soon as possible (preferably within 72 hours of study drug discontinuation) for an early study discontinuation visit. The following assessments should be completed at that visit:

- Physical examination (vital signs, weight).
- Complete blood count (red blood cell count, white blood cell count and differential, and platelet count).
- Fasting chemistry profile (alkaline phosphatase, ALT, AST, GGT, total bilirubin, creatinine, glucose, potassium, sodium, uric acid, lipid profile (total cholesterol, HDL-C, LDL-C, VLDL-C, triglycerides).
- CD4 cell count
- HIV-1 RNA in plasma: If the patient shows at any time a detectable viral load (> 50 copies/mL), the test should be repeated within 2 weeks for confirmation
- Quality of life questionnaires (MOS-HIV and EQ-5D)

- Questionnaires for assessing treatment adherence (GEEMA and VAS)
- Questionnaire for assessing treatment satisfaction (CESTA)
- Concomitant medications.
- Adverse events

### **8.2.6 Criteria for treatment discontinuation or modification**

Study medication should be discontinued if the following occurs:

- Underlying disease that may significantly affect assessments of clinical status in the investigator's judgment.
- Unacceptable toxicity (toxicity that compromises the ability to continue with the protocol-specific procedures).
- At the request of the subject.
- Pregnancy
- Therapeutic failure, defined as 2 VL measurements > 500 copies/mL at least 2 weeks apart in the experimental group and/or genotyping with PI mutations that prevent continued treatment with LPV/r monotherapy.

## **9. ADVERSE EVENTS AND MANAGEMENT OF TOXICITY**

### **9.1. ADVERSE EVENTS:**

#### **Definition of adverse events and categories of serious adverse events**

Investigators will routinely monitor all subjects during the study for detecting SAEs. An AE is defined as any untoward medical occurrence in a patient during treatment but that does not necessarily have a causal relationship with treatment. An AE may therefore be any untoward and undesired sign (such as an abnormal laboratory finding), symptom, or disease temporally associated to use of a medicinal product, whether or not the event is causally related to use of the product.

This event may occur due to use of the drug as stipulated in the protocol or to accidental or intentional overdose, abuse, or discontinuation of the drug. Any worsening of a pre-existing condition or disease is considered as an AE.

All adverse events will be recorded in the Case Report Form (CRF).

#### **Serious adverse event (SAE): definition and reporting procedure**

A serious adverse event (SAE) is any event that is fatal or life-threatening, requires or prolongs patient hospitalization, causes persistent or significant incapacity or disability, is a congenital anomaly or birth defect, or is a clinically significant event.

Clinically significant events are those that may not be immediately life-threatening, but are clearly clinically significant. They may jeopardize the subject or require intervention to prevent any serious outcome. Overdose or abuse of a drug will usually be considered as serious.

|                                        |                                                                                                                                                                                                                                     |
|----------------------------------------|-------------------------------------------------------------------------------------------------------------------------------------------------------------------------------------------------------------------------------------|
| Death                           | An event that results in patient death.                                                                                                                                                                                             |
| Life-threatening                | An event that, in the investigator's judgment, could have caused the immediate death of the patient if no medical intervention had occurred. This does not include the events that could have been fatal had they been more severe. |
| Hospitalization                 | An event that requires hospital admission, regardless of hospitalization time. This does not include emergency room visits or the stay at an outpatient center.                                                                     |
| Prolongation of hospitalization | An event that occurs while the study subject is hospitalized and prolongs hospital stay.                                                                                                                                            |

|                                                                                                          |                                                                                                                                                                                                                                                                                                                                                                                                                                                                                                                                                                                                                                                                                                                                             |
|----------------------------------------------------------------------------------------------------------|---------------------------------------------------------------------------------------------------------------------------------------------------------------------------------------------------------------------------------------------------------------------------------------------------------------------------------------------------------------------------------------------------------------------------------------------------------------------------------------------------------------------------------------------------------------------------------------------------------------------------------------------------------------------------------------------------------------------------------------------|
| Congenital anomaly                                                                                | An anomaly detected at or after delivery, or any anomaly causing fetal loss.                                                                                                                                                                                                                                                                                                                                                                                                                                                                                                                                                                                                                                                                |
| Persistent or significant disability or incapacity                                                | An event that causes a change significantly impairing the daily activities of a patient. Disability does not include experiences that have relatively little medical significance, such as headache, vomiting, diarrhea, flu, or accidental trauma (e.g. an ankle sprain).                                                                                                                                                                                                                                                                                                                                                                                                                                                                  |
| Medically important event requiring medical or surgical intervention to prevent a serious outcome | Medically important event that does not cause death or is immediately life-threatening and does not require hospital admission but which, based on medical judgment, involves a risk for the patient and requires medical or surgical intervention to prevent one of the above listed outcomes (patient death, life-threatening, hospital admission or prolongation of an existing hospitalization, congenital anomaly, or persistent or significant disability or incapacity). Examples of such events may include intensive treatment of an allergic bronchospasm at an emergency room or at the patient home, blood dyscrasias or seizures not leading to hospital admission of the patient, or development of drug dependence or abuse. |

### **Severity**

The physician will use the following definitions to rate the severity of each AE of special interest recorded as a study endpoint and for all SAEs.

|          |                                                                                                                               |
|----------|-------------------------------------------------------------------------------------------------------------------------------|
| Mild     | The adverse event is transient and easily tolerated by the patient.                                                           |
| Moderate | The adverse event causes discomfort to the patient and interferes with his usual activities.                                  |
| Severe   | The adverse event substantially interferes with the usual activities of the patient and may be disabling or life-threatening. |

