#### **8.1.2 Secondary endpoints:**

- Assessment of treatment satisfaction of HIV+ patients who start monotherapy with LPV/r tablets versus triple therapy containing any PI using the CESTA questionnaire (Spanish Questionnaire of Satisfaction with Antiretroviral Treatment) [21] from the baseline visit to study week 24.
- Assessment of treatment adherence by HIV+ patients who start monotherapy with LPV/r tablets versus triple therapy containing any PI using the GEEMA questionnaire [22] and a visual analog scale (VAS) [23].
- Assessment of regimen tolerability and safety in HIV+ patients who start monotherapy with LPV/r tablets versus triple therapy containing any PI.
- Proportion of patients with a viral load <50 copies/mL of HIV RNA at 24 weeks in HIV+ patients who start monotherapy with LPV/r tablets versus triple therapy containing any PI. A viral load >500 copies/mL of viral RNA (HIV-1) confirmed at study week 24 will be considered as virological failure.
- Changes in immune response in HIV+ patients who start monotherapy with LPV/r tablets versus triple therapy containing any PI, as measured through the change in CD4+ cell count from the baseline visit to study week 24

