| GEEMA Questionnaire                          |                 | X               | X*           | X             | X             | X                           |
| Adherence VAS                                |                 | X               | X*           | X             | X             | x                           |
| Concomitant medication                       |                 | X               | X*           | X             | X             | X                           |
| Adverse events                               |                 | X               | X*           | X             | X             | X                           |

(1) includes vital signs and weight measurement. Since adult patients will be enrolled, height will be measured at the baseline visit.

\*Only for patients in the experimental arm.

\*\*Record relevant data related to adverse events.

(2) Urine pregnancy test for women of childbearing age.

Any deviation from the protocol procedures should be reported to the sponsor and recorded in the Case Report Forms (CRFs).

All laboratory samples will be sent to local laboratories to be tested. The same local laboratory should be used throughout patient participation in the trial.

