### **Baseline visit:**

If laboratory data for confirming screening criteria have been obtained within two months of study recruitment and are available, the screening visit may be the same as the baseline visit.

The study drugs should start to be taken within 24 hours of the baseline visit. The following assessments should be available at the baseline visit:

- Physical examination (vital signs, height and weight).
- Quality of life questionnaires (MOS-HIV and EQ-5D)
- A negative urine pregnancy test for women of childbearing age.

- Complete blood count (red blood cell count, white blood cell count and differential, and platelet count).
- Fasting chemistry profile (alkaline phosphatase, ALT, AST, GGT, total bilirubin, creatinine, glucose, potassium, sodium, uric acid, lipid profile (total cholesterol, HDL-C, LDL-C, VLDL-C, triglycerides).
- CD4 cell count
- HIV-1 RNA in plasma: This will be measured in real time at the site using the standard virological methods at each site. The same methods should be used throughout the study for each subject.
- CESTA questionnaire to assess satisfaction with antiretroviral treatment.
- GEEMA questionnaire to assess treatment adherence
- VAS to assess treatment adherence
- Recording of concomitant medication
- Adverse events

Once the baseline visit procedures and assessments are reviewed, subjects will be centrally randomized at the study data center after data are received.

Patients randomized to group B will return for HIV RNA monitoring at treatment week 4 (+/- 2 days)

The following assessments should be completed at the **week 12 and week 24 visits or at the study discontinuation visit**. Study visits should be scheduled to occur within  $\pm 1$  week of the date specified for weeks 12 and 24, calculating the dates from the baseline visit:

- Physical examination (vital signs, weight).
- Complete blood count (red blood cell count, white blood cell count and differential, and platelet count)
- Fasting chemistry profile (alkaline phosphatase, ALT, AST, GGT, total bilirubin, creatinine, glucose, potassium, sodium, uric acid, lipid profile (total cholesterol, HDL-C, LDL-C, VLDL-C, triglycerides)
- CD4 cell count
- HIV-1 RNA in plasma: If the patient shows at any time a detectable viral load (> 50 copies/mL), the test should be repeated within 2 weeks for confirmation. Annex 1 provides suggestions for management of these cases
- Concomitant medication
- Adverse events

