### **Relationship with the drug**

The physician will use the following definitions to establish the causal relationship of each AE:

|                    |                                                                                                                                                                                                                             |
|--------------------|-----------------------------------------------------------------------------------------------------------------------------------------------------------------------------------------------------------------------------|
| Probably related   | The adverse event has a clear temporal relationship with the drug or recurs on drug rechallenge, and other cause is unlikely or significantly less likely.                                                                  |
| Possibly related   | The adverse event has a marked temporal relationship with the drug and is equally likely or less likely that another cause exists as compared to the possible relationship with the study drug.                             |
| Probably unrelated | The adverse event has a minimal or no temporal relationship with the drug or another more likely cause exists, or both.                                                                                                     |
| Unrelated          | The adverse event is due to an underlying or concomitant disease or to the effect of another drug, and is not related to the drug (e.g. has no temporal relationship to the drug or another much more likely cause exists). |

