## **9.2. MANAGEMENT OF TOXICITY:**

All clinically significant laboratory toxicities will be managed according to the ACTG classification of adverse event severity (version 1.0 December 2004) (Appendix 5).

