### ***Sample size and rationale***

In a similar study population (e.g. HIV+ patients with an undetectable viral load, i.e. < 50 copies/mL of HIV-1 RNA), the mean baseline quality of life score measured with the MOS-HIV questionnaire was 61.84 [24]. As standard deviation is not available, we assume for all calculations that standard deviation will be the highest score minus the lowest score in the quality of life dimension (e.g. 100) divided by 5, which gives 20. This standard deviation of 20 is the same as found in HIV-infected asymptomatic patients, patients with AIDS-related symptoms, or patients with AIDS and a CD4 cell count <100 [25]. Assuming, then, that quality of life will remain unchanged in patients assigned to the control group (maintaining current antiretroviral therapy) and will improve by 10% (e.g. to scores of 68.02) in patients assigned to the experimental group (LPV/r® as monotherapy), with a 1:2 ratio, an 80% statistical power, and a two-sided alpha of 0.05, 372 patients would be required, 248 randomized to the experimental group and 124 randomized to continue on the current antiretroviral therapy.

Assuming 7% follow-up losses, the final sample size required will be of 260 patients for the experimental group and 130 patients for the control group, i.e. a total of 390 patients.

Because the triple antiretroviral therapy based on a PI boosted with ritonavir (control treatment) has been widely studied for a practical sense, it has been considered to allocate the sample to twice the experimental treatment (1:2, respectively) [24 ], [26].

This distribution of the sample (1:2) compared with the distribution of equal groups (1:1) ensures greater security in the contrast of the study to a possible greater variability of response in the quality of life in the experimental group since this group is expected to more patients with diarrhea to begin new therapy. [27]

Also it will provide an improved accuracy in estimating mean and smaller confidence intervals, for example, more than 1% in the estimated proportions near 50%.

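### Severity grading is assured only for SAEs and an unnamed set of special-interest events, and an ambiguous footnote leaves full entry of the scheduled laboratory values unassured

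*Protocol*

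**What the plan says.** **Severity.** Section 9.1 (Severity) gives a three-level scale of mild, moderate and severe. The physician uses it to "rate the severity of each AE of special interest recorded as a study endpoint and for all SAEs".

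**Recording and causality.** The same section is broader on its other two requirements. On recording: "All adverse events will be recorded in the Case Report Form (CRF"). On causality: "The physician will use the following definitions to establish the causal relationship of each AE".

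**Laboratory toxicity.** Section 9.2 states: "All clinically significant laboratory toxicities will be managed according to the ACTG classification of adverse event severity".

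**Laboratory data.** In the schedule in 8.2.1, two rows carry a double asterisk: chemistry and the row labelled Hepatology. I take the latter to be the blood count, since the visit lists contain a complete blood count and no separate liver panel. The footnote reads "Record relevant data related to adverse events". The visit lists in 8.2.3 and 8.2.5 require a blood count and a fasting chemistry profile, including the "lipid profile (total cholesterol, HDL-C, LDL-C, VLDL-C, triglycerides"), at baseline, weeks 12 and 24, and early discontinuation.

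**What the data are for.** Section 8.1.2 lists as a secondary endpoint "Assessment of regimen tolerability and safety in HIV+ patients who start monotherapy with LPV/r tablets versus triple therapy containing any PI". The sample size section partly justifies the 1:2 allocation by saying that "this group is expected to more patients with diarrhea to begin new therapy". Section 12.1 defines population A.2 by removing patients who left the study because of diarrhoea.

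**The concern.** A grade that was never assigned, or a laboratory value that was never entered, cannot be recovered by an analysis plan. This is a matter of what the protocol fixes for data collection, so it does not wait on the SAP.

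Diarrhoea is the one adverse event the protocol expects to differ between arms, and it affects both the allocation rationale and an analysis population. If its non-serious episodes are ungraded, a mild passing episode and a troublesome but non-serious one look the same in a severity table. If sites decide for themselves which events are of special interest, grading may differ by site or, since the trial is open label, by arm.

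Section 4.1 gives hyperlipidaemia as one of the metabolic harms of triple therapy. A comparison of mean lipid change needs normal values as well as abnormal ones. If investigators who know the allocation choose which results are relevant enough to enter, that comparison is open to bias even though every sample was drawn.

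**Working it through.** No figure in the protocol bears on this point, so the check is mainly a comparison of the text.

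**Step 1: who gets a severity grade?**

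| Requirement in 9.1 | Scope |
|---|---|
| Entry in the CRF | all adverse events |
| Causality | each adverse event |
| Severity | SAEs, plus special-interest events recorded as an endpoint |

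The severity scope is narrower than the other two and depends on a set of events that must be defined elsewhere. The endpoint lists in 8.1.2 and 12.3 refer to tolerability and safety in general and name no event. Read strictly, the non-serious part of the graded set is empty. Read loosely, each site fills it.

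**Step 2: does another section close the gap?** Section 9.2 applies the ACTG classification to the management of laboratory toxicities, not to the recording of clinical events. The Intolerance paragraph in section 7 refers to a section 7.7, but section 7 ends at 7.4. Neither gives a grading rule for non-serious clinical events.

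**Step 3: would diarrhoea be graded as an SAE?** It would if it met a seriousness criterion such as hospital admission. Under the disability criterion, however, 9.1 lists diarrhoea among experiences of little medical significance. Most episodes can therefore be expected to be non-serious and to have no assured grade.

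**Step 4: what does the footnote govern?** It is attached to the blood count and chemistry rows, while the HIV RNA and CD4 rows have none. The visit lists say the tests must be done, but not that every value goes into the CRF. Two readings fit: flag results that bear on adverse events in addition to entering everything, or enter just those results. The text does not settle which.

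**Step 5: how many panels does the ambiguity touch?** Planned enrolment is 390 (section 6.1), with scheduled panels at baseline, week 12 and week 24:

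390 × 3 = 1,170 panels at full enrolment and full attendance.

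This counts panels whose entry is unclear. It does not count panels lost.

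**The case against.** A reader might infer three stronger things, and the documents support none of them.

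- **That laboratory data are recorded exclusively when linked to an adverse event.** The footnote contains no such restriction. The tests are required in both arms at the same visits, and 9.1 counts an abnormal laboratory finding as an adverse event in its own right. Untoward lipid, liver or renal values should thus reach the CRF even under the narrow reading. The table's note keys also look unreliable: the note keyed to chemistry describes the pregnancy test. What remains in doubt is whether all values, normal ones included, are entered.
- **That the arms cannot be compared on diarrhoea or lipids.** Adverse events are scheduled in both arms at baseline, weeks 12 and 24, and discontinuation. Causality is rated for each, and reasons for withdrawal are recorded. Incidence, relatedness, seriousness and discontinuation stay comparable. The extra week 4 assessment in the experimental arm raises a separate question about ascertainment, which grading would not cure. Lipid changes can be compared if the values are captured.
- **That most safety laboratory data would be lost.** Any such figure needs an assumed share of panels linked to adverse events, and the protocol gives none. Results also remain in local laboratory records.

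It can also be argued that, because safety is itself a secondary endpoint, every adverse event is recorded as a study endpoint and so is graded. That reading is possible, but it leaves the special-interest qualifier without effect. The CRF and Appendix 5 are not shown and may resolve some of this in practice. The objection narrows the point considerably but leaves two real gaps in the wording.

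**Conclusion.** The point holds in limited form. As written, severity grades are assured for SAEs and for no identifiable non-serious event, so the severity of non-serious diarrhoea may not be comparable between arms. The footnote is ambiguous, so an unbiased comparison of mean laboratory changes is not assured. It is not shown to be impossible.

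The size cannot be stated as a bias or a loss of power. Its extent is every non-serious clinical adverse event, for the grade, and up to 1,170 scheduled panels, for laboratory entry. The conclusion assumes that sites follow the protocol text and that an unseen CRF does not already ask for more. It is an inexpensive improvement to a stated collection rule, in support of a stated secondary objective; the primary quality-of-life comparison does not depend on it.

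**What to change.** 1. In 9.1 (Severity), require a rating for every adverse event in both arms on the mild/moderate/severe scale already printed there, so that its scope matches that of the causality rating. A list of special-interest events is then not needed for grading.
2. In 8.2.1, reword the double-asterisk footnote so that all scheduled blood count and fasting chemistry values at baseline, week 12, week 24 and early discontinuation are entered in the CRF, whether or not they relate to an adverse event. Any instruction to flag results related to adverse events can stand as an addition.

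The cost is revised protocol and CRF wording and some extra data entry at sites, for results the local laboratories already report. No test, visit or sample is added.
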